##### Notes review

A review of medical records will be undertaken to document return visits to GP practices/walk-in centres and out-of-hours clinics with a respiratory infection in the 28 days following recruitment. In addition, resource use information will be extracted for each patient including medication, primary care visits, outpatient visits, and hospital admissions.

All trial procedures are depicted in the SPIRIT figure [32] shown in Table 3.

**Table 3 Tab3:** SPIRIT figure for HATRIC trial

Observation/procedure	Person undertaking the specified event	Timings of visit/contact				
		Screening/registration D1	D2-3	D14	D28	D35
Informed consent	GP/nurse^1^/HCA^1^/CTA^1^	X				
Inclusion/exclusion criteria	GP/nurse prescriber^1^	X				
Baseline symptoms^2^	GP/nurse	X				
Relevant medical history	GP/nurse	X				
Vital signs^3^	GP/nurse	X				
Issue trial medication	GP/nurse	X				
Issue patient diary	GP/nurse	X				
Completion of patient diary (days 1–28)	Patient	X	X	X	X	
Phone call to patient (diary assessment)	SCTU		X	X	X	Only if diary not returned or incomplete
Completion of diary by recall	Patient/SCTU					X
Adverse event notification^4^	Patient/SCTU		X	X	X	
Adverse event (AE) assessing	GP		X	X	X	
AE recording/reporting^4^	GP/nurse		X	X	X	
Concomitant medication (only to be recorded in the event of an SAE and specified AEs)	GP/nurse		X	X	X	
SAE assessing	GP		X	X	X	
SAE reporting	GP/nurse		X	X	X	
Medical note review	GP/nurse				X	

^1^In line with local GP surgery procedures with demonstrable and appropriate level of training. Specific duties delegated by the PI

^2^The severity of cough, phlegm, shortness of breath, wheeze, blocked or runny nose, chest pain, muscle aches, headaches, disturbed sleep, general feeling of being unwell, fever, and interference with normal activities

^3^Blood pressure; heart rate; temperature; oxygen saturation levels (Sats); C-Reactive protein (CRP), if measured; and the presence of wheeze or crackles in the chest

^4^Patients will be asked to notify their GP/nurse of specified adverse events. In addition, specified adverse events that are discovered by SCTU staff during patient contact phone calls will be notified immediately to GP/nurse. Reporting and recording of all AEs is carried out by GP/nurse. NB: the Patient is free to withdraw consent at any time without providing a reason. When withdrawn, the patient will continue to receive standard clinical care. Follow-up data will continue to be collected (unless the patient has specifically stated that they do not want this to happen)

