#### Follow-up

##### Patient symptom diary

Patients will complete daily diary data for up to 28 days after presentation. They will be asked to stop completing the diary 2 days after complete resolution of symptoms. The collection of diary scores will not be limited to the time during which study medication is being used, to allow the capture of total symptom duration. The diary has previously been validated and is sensitive to change and internally reliable [25, 26].

Patients will also keep a record of the number of times trial medication has been taken every day and, if applicable, when antibiotics or other treatments for their chest infection were taken. Patients will also be asked questions about resource use for their acute bronchitis, including consultations with healthcare professionals in secondary care, medications purchased, and absences from work.

All patients will complete the EQ-5D-5L questionnaire at baseline (day 1) and day 7, and half of the patients will also be randomly selected to complete the questionnaire at additional time points on day 2 and day 4. This will allow us to assess the acceptability of the frequency in collecting quality of life data.

After recruitment, patients will be contacted after 1–2 days to check for any problems with diary completion. Patients will be contacted again after 14 and 28 days to prompt diary completion and return. In the event of diaries not being returned, a brief telephone interview to collect the key data will be undertaken after 35 days. Patients will also be contacted in the event that a diary is returned incomplete, to obtain missing key data.

Contact with patients at each time point will be made initially by text or email, if the patient has provided a mobile telephone number or an email address, to explain when we will be calling and then by telephone.

Completed diaries will be returned to the Southampton Clinical Trials Unit in a freepost envelope. To improve the return rate of completed diaries, patients who return a fully completed diary or complete a diary by recall will receive a £5 shopping voucher to thank them.

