### Adverse event reporting

All serious adverse events and specified non-serious adverse events occurring up until 28 days post-randomisation will be reported. Patients will carry a study card, which highlights the need to notify the recruiting GP/nurse regarding adverse events. Information about the adverse event will be transcribed into the patients’ medical records and reported to the SCTU as required.

Non-serious adverse events will only be recorded if due to any medical encounters related to the following:Chest symptoms: any events relating to cough, chest pain, or other symptoms of lower respiratory tract infection or their complications (including sepsis)Medication: any events relating to study medication

The general practitioners providing care for the patient are advised to record any event for which there is uncertainty as to whether it is study related or not, and to discuss with the chief investigator (CI).

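### Table 3 puts the only medical note review at day 28, just as the 28-day period it must cover is closing, and marks no adverse event enquiry at the day-35 call

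*Protocol article*

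**What the plan says.** Four places in the protocol article bear on this.

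- **Safety window (Adverse event reporting).** "All serious adverse events and specified non-serious adverse events occurring up until 28 days post-randomisation will be reported".
- **Notes review (text).** The review is to be done "to document return visits to GP practices/walk-in centres and out-of-hours clinics with a respiratory infection in the 28 days following recruitment". The text gives this look-back period but no date for doing the review. It also states that "resource use information will be extracted for each patient including medication, primary care visits, outpatient visits, and hospital admissions".
- **Table 3.** The row "Medical note review" has a single mark, under D28. The row "Adverse event notification^4" and the rows for assessing and reporting adverse events and serious adverse events are marked at D2-3, D14 and D28 and left empty at D35. The phone-call row does have a D35 entry: "Only if diary not returned or incomplete". Footnote 4 adds that "specified adverse events that are discovered by SCTU staff during patient contact phone calls will be notified immediately to GP/nurse", and it names no particular call.
- **Day-35 contact (Patient symptom diary).** "In the event of diaries not being returned, a brief telephone interview to collect the key data will be undertaken after 35 days". Patients who send back an incomplete diary are also contacted for the missing key items. Adverse events are not mentioned as a purpose of this contact.

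**The concern.** A retrospective record review is only as complete as the record on the day it is read. Several of the contacts this review must find (walk-in centre, out-of-hours, outpatient, hospital) arise outside the practice and have to be transmitted to it. A review held as the look-back period closes allows no time for that, so contacts from the last days are the ones most likely to be absent.

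The D35 call could pick up some of them by asking the patient, since it comes after the window has closed. A caller who follows Table 3 would have no prompt to ask.

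Two outputs are affected. One is the safety count, which the Trial Steering Committee oversees in place of a separate data monitoring committee. The other is resource use. Under the Health economic analysis plan it comes mainly from the case notes and the diaries, and whether enough of it can be collected is one of the listed feasibility questions.

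**Working it through.** The plan states no figure on this point that could be reproduced. The check is a day count followed by a comparison of the capture routes.

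**Day count.** Table 3 labels screening and registration D1, so elapsed days at column Dk = k − 1.

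- D14: 14 − 1 = 13 elapsed days.
- D28: 28 − 1 = 27 elapsed days.
- D35: 35 − 1 = 34 elapsed days.

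The look-back period and the safety window both end at 28 elapsed days. The time left for outside contacts to reach the record is the review day minus 28:

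- Review at D28, column read literally: 27 − 28 = −1 day.
- Review at D28, read as 28 full days (the text places its calls after 14 and 28 days): 28 − 28 = 0 days.
- Review at D35: 34 − 28 = 6 days, or 35 − 28 = 7 days on the second reading.

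The mismatch in dates is therefore at most about one day. What matters is that the allowance for record lag is nil on either reading.

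**Other routes for an event late in the window.**

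- *Study card.* Open throughout, but it depends on the patient reporting.
- *Scheduled calls at D2-3, D14 and D28.* Marked for adverse events. The last one has the same timing as the notes review.
- *Diary.* Patients stop two days after symptoms resolve, so a later re-consultation may not be entered. Its resource questions name secondary-care consultations, purchases and work absence. Return visits to the practice, walk-in centre and out-of-hours clinic are assigned to the notes review.
- *D35 call.* Made only when the diary is missing or incomplete, and its stated purpose is key diary data. Footnote 4 would pass on an event that came to light, but it does not require the caller to ask.

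**Table 3 against its footnote.** Footnote 4 applies to patient contact calls without limit by day, and D35 is one of those calls. The row that carries the footnote is nevertheless blank at D35.

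**Size.** A count of missed events would need an event rate late in the window, a lag for entry into the practice record and a contact-failure rate. The documents give none of the three, so no number or share can be calculated.

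**The case against.** The strongest reply is that D28 is a nominal label. A review defined by a 28-day look-back cannot sensibly be finished before 28 days have passed, the text speaks of calls after 28 and after 35 days, and visit windows may be set in the full protocol, which is not shown. The reporting window also closes at 28 days, so empty adverse event cells at D35 can be read as consistent with it. This narrows the point but does not remove it. Even on the nominal reading, the review is timed at the close with no allowance for lag, and an event with onset inside the window can still be learned of after it.

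The consequence is also small. The analysis is descriptive with no group comparison, Table 1 has no safety objective, and treatment is capped at two weeks, so roughly the second half of the window follows the longest permitted treatment. That stands, and it is why the point is minor.

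A reader might infer more than the documents support:

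- *That late events are lost mainly in patients who are hard to reach.* The D35 call is triggered by diary status, not by failed phone contact, and notes are extracted for every patient whether or not anyone reached them by phone. A lag in the record would affect responders too.
- *That for a patient last reached at day 14, the remaining 14 of 28 days rest on the notes review alone.* The study card stays in force, and in-scope non-serious events arise from medical encounters and are recorded by the GP or nurse.
- *That the D35 call rules out adverse event capture.* Footnote 4 gives a route. What is missing is a scheduled enquiry.
- *That the harm can be sized from diary non-return.* If 20% to 40% of diaries were missing or incomplete (an assumption), 0.20 × 160 = 32 to 0.40 × 160 = 64 patients would be due a D35 call. That counts calls, including patients fully contacted at D28. It does not count missed events.

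**Conclusion.** The point holds as a minor one. Table 3 times the only notes review at the close of the 28-day period, or about one day before it, and leaves adverse event and serious adverse event enquiry unmarked at the one scheduled contact clearly after the close, out of step with its own footnote 4.

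The likely result is a modest undercount of late events and resource use. This rests on two assumptions: that sites follow Table 3 as printed, and that some outside contacts take more than a day or so to reach the practice record. The documents give no data on the second, so the size stays unknown. Allocation is blinded and 1:1, and nothing suggests that the loss would differ between active and placebo.

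**What to change.** Make two edits to Table 3, with matching wording in the Notes review text and the call script.

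1. Move the medical note review to a point after the 28-day window has closed, for example on or after D35. Keep the look-back unchanged and say in the text that the review is done once the window has closed.
2. Mark adverse event notification, assessing and reporting, and serious adverse event assessing and reporting, at the D35 call for events with onset up to day 28. This brings the table into line with footnote 4.

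Both activities are already planned, so no new contact is needed. The cost is that the review is completed about one week later (35 − 28 = 7 days) and the D35 script is slightly longer. The same timing should carry into the definitive trial.

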#### Trial discontinuation

In consenting to the study, patients will have consented to the study intervention, follow-up, and data collection. Patients may be discontinued from the study procedures at any time.

Patients may be discontinued from the study in the event of:Clinical decision, as judged by the principal investigatorThe development of toxicity, regardless of causality, which, in the investigator’s opinion, precludes further treatment under this protocolThe patient withdraws consentThe recruiting physician’s judgement due to medical reason, e.g. concurrent illness, pregnancy.Non-compliance with protocol

Full details of the reason for trial discontinuation will be recorded in the end of study electronic case report form (eCRF) and medical record. Recruiting physician’s judgement refers to the discontinuation of patients due to a clinical judgement made post-randomisation but whilst carrying out the recruitment and baseline trial processes for a patient, for example, if a patient is found to be ineligible whilst having their full history taken and examination carried out. At any other time within the trial, a patient discontinued due to clinical judgement should be listed as a discontinuation due to a clinical decision, for example, if a patient develops symptoms that could be a side effect of the trial medication.

#### Withdrawal

The patient will be free to withdraw consent from the study at any time without providing a reason. Investigators will explain to patients the value of remaining in trial follow-up and allowing this data to be used for trial purposes so that where possible, patients who have withdrawn from trial treatment will remain in follow-up as per the trial schedule. If patients additionally withdraw consent for this, they will revert to standard clinical care as deemed by the responsible clinician. It would remain useful for the trial team to continue to collect standard follow-up data, and unless the patient explicitly states otherwise, follow-up data will continue to be collected. Details of withdrawal (date, reason if known) will be recorded in the end of study eCRF and medical record.

#### End of trial

The end of the trial will be when the last patient has had their last data that answers the research question collected and verified.

#### Unblinding procedures

Any emergency clinical decisions required will not be affected or altered by knowledge of the treatment group allocated to the patient. If unblinding is required, this can be done by the trial statisticians at the SCTU.

### Treatments

Primary care sites will be randomised to one of two groups (tablet or liquid preparation), and within each site, patients will be randomised to active or placebo IMP.

This will result in four treatment groups:Liquid *Pelargonium sidoides* root extract EPs®7630—30 drops 3× daily, to be taken 30 min before mealsLiquid placebo—30 drops 3× daily, to be taken 30 min before mealsTablet *Pelargonium sidoides* root extract EPs®7630—one 20 mg tablet 3× daily, to be taken 30 min before mealsTablet placebo—one 20 mg tablet 3× daily, to be taken 30 min before meals

The tablets, liquid, and matching placebos will be provided and packaged ready for distribution to sites by [name] GmbH & Co. KG, Karlsruhe (Germany).

Patients will be asked to take the IMP daily until 2–3 days after symptoms have resolved, but treatment duration should not exceed 2 weeks. If a dose is missed, the patient should not take twice the dose but continue to take their usual dose at the usual time.

The use of the delayed prescription strategy for antibiotics will be encouraged (because it reduces use of antibiotics whilst maintaining patient satisfaction [27]), but clinicians will be able to offer one of three following antibiotic strategies in addition to the randomised intervention:Immediate antibioticsDelayed antibioticsNo antibiotics

No class of antibiotic has been shown to have superior performance to another in the treatment of LRTI/acute bronchitis, and hence, the prescribing physician will prescribe delayed antibiotics according to local guidelines. Patients will be asked to wait 7–10 days before collecting the delayed prescription unless their symptoms show substantial deterioration.

### Accountability

HATRIC trial medication will be stored centrally and distributed to GP sites by the SCTU. Drug accountability logs will be maintained by the SCTU and at individual sites. Additionally, patients will be asked to record trial medication usage in their patient diary and to return all unused IMP and packaging to the research team.

### Data collection

The majority of patient data will be entered by research staff at site via a remote data collection tool (Medidata Rave). Diary data will be entered into the trial database by the research team. All data will be retained in accordance with the General Data Protection Regulations. The PI is responsible for ensuring the accuracy, completeness, and timeliness of the data entered.

Data will be checked for missing or unusual values (range checks) and checked for consistency within patients over time by SCTU staff. Any discrepant data collected at site will be returned to the site in the form of electronic data queries. Queries regarding the diary data will be discussed with patients as outlined above in the patient follow-up section. Full details on data management procedures are available in the HATRIC Data Management Plan, available on request.

All other processes relating to the storing of trial data, trial monitoring and audit, and archiving will follow standard GCP procedures.

### Adverse event reporting

All serious adverse events and specified non-serious adverse events occurring up until 28 days post-randomisation will be reported. Patients will carry a study card, which highlights the need to notify the recruiting GP/nurse regarding adverse events. Information about the adverse event will be transcribed into the patients’ medical records and reported to the SCTU as required.

Non-serious adverse events will only be recorded if due to any medical encounters related to the following:Chest symptoms: any events relating to cough, chest pain, or other symptoms of lower respiratory tract infection or their complications (including sepsis)Medication: any events relating to study medication

The general practitioners providing care for the patient are advised to record any event for which there is uncertainty as to whether it is study related or not, and to discuss with the chief investigator (CI).

### Sample size

The sample size for this study will be 160 patients overall or 40 patients per arm (4 arms in total) recruited from 20 sites. Eighty patients will receive the liquid formulation either active or placebo, and 80 will receive the tablet formulation either active or placebo in a 1:1 allocation ratio.

No formal sample size calculation was carried out; however, ignoring clustering, using a 95% confidence interval approach and an expected proportion of 50% of eligible patients randomised into the trial (to give the worst-case scenario), it can be shown that this sample size allows us to predict the recruitment rate to within 8% using nQuery Advisor v7.0.

Accounting for the clustering based on an intra-cluster correlation (ICC) of 0.05 and an expected proportion of 50% of eligible patients randomised into the trial, it can be shown that this sample size allows us to predict the recruitment rate (number of eligible patients randomised into the trial) to within 13%, given an average cluster size of 8 and 20 recruiting sites. Based on an ICC of 0.1, the sample size would allow us to predict the rate to within 14% [28].

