### Objectives

The aim of this study is to determine the feasibility of conducting a fully powered trial of *Pelargonium sidoides* root extract as an alternative to inappropriate use of antibiotics for lower respiratory tract infections in UK primary care. Specific feasibility objectives are detailed below (see Table 1).

**Table 1 Tab1:** Feasibility objectives and endpoints for the HATRIC trial

Feasibility objective	Endpoint used to evaluate
Eligibility: number of patients included and number excluded (+ reasons) from the trial	On site screening logs
Recruitment: ability to recruit patients into the intervention from those attending primary care	On site enrolment records—monthly rate/site adjusted for site list size
Randomisation: willingness to be randomised	Proportion of eligible patients recruited
Retention: across the duration of the intervention and return of a fully completed diary	Quantitative data from enrolment Withdrawal rate from study Completion of outcome measures
Intervention compliance	Diary data and returned medication
Patient preference for liquid/tablet formulation	Diary data Returned medication Recruitment data
Establish the frequency of collecting EQ5D questionnaire and identifying the key resources associated with the intervention and potential influence on service usage Establish methods of data collection for the health economics analysis	Development of health economic protocol and collection of outcome data EQ-5D-5L questionnaire and case note review
Acceptability of the patient diaries, patients’ willingness to complete them, and the importance of telephone/text contact	Quantitative data collection—percentage of patients returning completed diaries
Success of delayed antibiotic strategy	Diary data on day antibiotics commenced
Need for stratification by antibiotic strategy in main study	Proportion allocated to immediate and delayed antibiotic strategy
To inform sample size for future trials	Rate of outcome measures in the control group
Quality of life measurements and resource use	Identify the key resource items to be collected and how often to collect EQ-5D-5L in the full trial

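### The 8% precision for the proportion of eligible patients randomised uses the 160 randomised as its denominator, and the clustered 13% and 14% do not follow from the stated 20 sites of 8

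*Protocol article*

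**What the plan says.** The Sample size section fixes the size of the trial: "The sample size for this study will be 160 patients overall or 40 patients per arm (4 arms in total) recruited from 20 sites". It splits the 160 by formulation and then by treatment; for tablets, "80 will receive the tablet formulation either active or placebo in a 1:1 allocation ratio". These are therefore patients who have been allocated to an arm.

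The section says that no formal calculation was done. In its place it gives the precision of one proportion, "using a 95% confidence interval approach" and "an expected proportion of 50% of eligible patients randomised into the trial (to give the worst-case scenario". Three figures follow:

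- ignoring clustering: "this sample size allows us to predict the recruitment rate to within 8% using nQuery Advisor v7.0";
- at an ICC of 0.05: "to within 13%, given an average cluster size of 8 and 20 recruiting sites";
- at an ICC of 0.1: "Based on an ICC of 0.1, the sample size would allow us to predict the rate to within 14" (per cent).

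Table 1 in the Objectives section gives the matching endpoint for willingness to be randomised: "Proportion of eligible patients recruited".

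**The concern.** The proportion has randomised patients on top and eligible patients underneath. The 160 belongs on top. If it is used underneath, the stated precision belongs to a different study, one that approaches 160 eligible patients and randomises about 80 of them. The cluster size of 8 raises the same question, because 8 × 20 = 160 again counts randomised patients.

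The three half-widths are the only quantitative support that the article gives for 160. They also describe how well the trial will estimate a quantity needed to plan the definitive trial. A reader who plans from them, or reuses the method, would be misled about that precision. A second question is whether the clustered figures follow from the inputs printed beside them, whichever denominator was intended.

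**Working it through.** **Inputs** (Sample size section, except the endpoint, which is in Table 1): 160 randomised; 20 sites; average cluster size 8; expected proportion p = 0.50; ICC 0.05 and 0.10; 95% interval, taken as two-sided (assumption); endpoint randomised/eligible.

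**Formula.** Half-width = 1.96 × √[p(1−p)/n × DE], with design effect DE = 1 + (m−1) × ICC, where n is the number in the denominator and m the number per site. DE = 1 when clustering is ignored.

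**1. Reproducing the 8%.** With n = 160: 1.96 × √(0.25/160) = 7.75%, which rounds to 8%. With a continuity correction it is 8.06%, and Clopper-Pearson gives 8.0%. The stated figure therefore has 160 in the denominator.

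**2. The denominator that the plan implies.** 160/0.50 = 320 eligible patients, or 320/20 = 16 per site. Then 1.96 × √(0.25/320) = 5.5%. Other standard intervals at n = 320 lie between 5.45% and 5.6%, so the choice of interval does not bring back 8%. A simulation that stops when 160 have been randomised also gives 5.5%.

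**3. Worst case.** With 160 randomised fixed, n = 160/p, and the variance ignoring clustering is p²(1−p)/160. This peaks at p = 2/3, not at 0.5. There n = 240 and 1.96 × √[(2/9)/240] = 6.0%. Other values are 2.8% at p = 0.2, 4.8% at 0.4, 5.9% at 0.6 and 5.5% at 0.8. Ignoring clustering, 8% is not reached at any proportion.

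**4. Trying to reproduce the 13% and 14%.**

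| n | m | ICC 0.05 | ICC 0.10 |
|---|---|---|---|
| stated | 8 | 13% | 14% |
| 160 | 8 | 9.0% (DE 1.35) | 10.1% (DE 1.70) |
| 160, t on 19 df | 8 | 9.6% | 10.8% |
| 80 | 8 | 12.7% | 14.3% |

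With m = 8, only totals from 78 to 82 round to both 13% and 14%. With n = 160, no single cluster size gives both. A half-width that rounds to 13% needs DE between (12.5/7.75)² = 2.60 and (13.5/7.75)² = 3.03, so m−1 between 32 and 41 at ICC 0.05. One that rounds to 14% needs DE between 3.03 and (14.5/7.75)² = 3.50, so m−1 between 20 and 25 at ICC 0.10. These ranges do not overlap.

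**5. Clustered figures on the implied denominator** (n = 320, m = 16, 20 equal sites):

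- ICC 0.05: DE = 1 + 15 × 0.05 = 1.75; half-width 7.2% with z, 7.7% with t on 19 df.
- ICC 0.10: DE = 1 + 15 × 0.10 = 2.50; half-width 8.7% with z, 9.2% with t on 19 df.
- Maxima over p with 160 randomised fixed (n = 160/p, m = 8/p): about 7.5% and 8.8% with z, both near p = 0.6.

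**The case against.** The best defence is that nothing is at risk. The half-width ignoring clustering is at most about 6.0%, so a claim of 8% stays true as an upper bound. Likewise 7.5% and 8.8% lie inside 13% and 14%. The Statistical analysis plan section says that no formal progression criteria were set, and the question on the proportion recruited has no threshold that a half-width could move. The reported interval will come from the screening and enrolment records, not from this paragraph. All of this stands, and it limits the severity. It does not make the figures correct: they are presented as the precision that this sample size gives.

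One might also read 160 as the number of eligible patients, which would make 8% right. Then about 80 would be randomised, or 20 per arm, against the stated 40.

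The worst-case label is right for a fixed denominator. With the numerator fixed it is wrong, but the shift is small: 5.5% to 6.0%, 7.2% to 7.5% and 8.7% to 8.8%.

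A reader might infer that the one mix-up explains all three figures. It does not, since 160 patients in clusters of 8 give 9.0% and 10.1%. A reader might also infer that the clustered figures were worked out for one formulation group, 80 patients in 10 sites. The arithmetic fits, but the section gives 20 sites, and the method rests on a cited source that is not at hand. How 13% and 14% were obtained is unknown.

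**Conclusion.** Two separate errors stand, both moderate.

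- The 8% takes the number randomised as the denominator of a proportion among eligible patients. On the plan's own 50% the figure is 5.5%, and at most about 6.0%. This rests on a two-sided 95% interval and on 160 being the number randomised, which the four arms of 40 establish.
- The 13% and 14% contradict the 160 patients, 20 sites and cluster size of 8 printed with them. Those inputs give 9.0% and 10.1%. On the eligible denominator the figures are about 7.2% and 8.7% with z, or 7.7% and 9.2% with t, if there are 20 sites of equal size.

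Both errors are conservative, because precision is understated. It would be wrong to conclude that the trial is too small, that more patients are needed or that its feasibility is in doubt. For proportions among randomised patients, such as retention or diary return, 160 is the correct denominator.

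**What to change.** Rewrite the precision paragraph in the Sample size section along these lines:

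> If half of eligible patients are randomised, 160 randomised corresponds to about 320 eligible patients, or about 16 per site in 20 sites. The 95% half-width for the proportion of eligible patients randomised is then 5.5% without allowance for clustering, about 7.2% at an ICC of 0.05 and 8.7% at an ICC of 0.10 (7.7% and 9.2% using t on 19 degrees of freedom). These values assume 20 sites of equal size; unequal sizes or fewer sites widen them.

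The caveat on sites is needed because the Abstract gives an approximate number of sites and the section on participants and enrolment gives twenty as an upper limit.

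Either drop the worst-case label or give the maxima with 160 randomised: about 6.0%, 7.5% and 8.8% with z. Name the quantity as the proportion of eligible patients randomised throughout, because Table 1 uses recruitment for the monthly rate per site. If 13% and 14% were meant for some other quantity or subgroup, say which and give its n and number of clusters.

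The cost is one paragraph of text. The number recruited does not change.

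### The cluster-adjusted precision of 13% and 14% does not follow from the stated inputs: 160 patients in 20 sites of 8 give about 9% and 10%

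*Protocol article*

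**What the plan says.** The Sample size section of the protocol article sets the target: "The sample size for this study will be 160 patients overall or 40 patients per arm (4 arms in total) recruited from 20 sites". It states that there was no formal calculation and offers three precision figures for the proportion of eligible patients who are randomised.

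- **Ignoring clustering.** The basis is "using a 95% confidence interval approach and an expected proportion of 50% of eligible patients randomised into the trial", with 50% chosen as the worst case. The result is that "this sample size allows us to predict the recruitment rate to within 8% using nQuery Advisor v7.0".
- **ICC 0.05.** "Accounting for the clustering based on an intra-cluster correlation (ICC) of 0.05" and the same 50%, the article says that "this sample size allows us to predict the recruitment rate (number of eligible patients randomised into the trial) to within 13" per cent, "given an average cluster size of 8 and 20 recruiting sites".
- **ICC 0.1.** "Based on an ICC of 0.1, the sample size would allow us to predict the rate to within 14" per cent.

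Both clustered sentences refer to the sample size just described. Neither mentions a formulation group or any other subset.

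**The concern.** The stated inputs are complete and agree with one another (20 sites × 8 patients = 160), so the clustered figures can be checked directly. Set beside the unclustered 8%, a half-width of 13% implies that an ICC of 0.05 widens the interval by 13/8, or about 1.6 times. With only 8 patients per site, that is far more than such an ICC should do.

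These three figures are the only quantitative support for recruiting 160 patients. The analysis rests on estimation, and the proportion of eligible patients recruited is both a Table 1 endpoint and one of the listed feasibility questions. A reader planning the definitive trial from this section would take away the wrong precision and the wrong price for clustering.

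**Working it through.** **Inputs, all from the Sample size section:** n = 160; 20 sites; average cluster size m = 8; p = 0.5; 95% interval (z = 1.96); ICC = 0.05 or 0.1.

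**Formula:** half-width = z × √[p(1 − p)/n × DE], with design effect DE = 1 + (m − 1) × ICC.

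**Step 1: reproduce the unclustered figure.** 1.96 × √(0.25/160) = 7.7%, which rounds to the printed 8%. This figure is right and uses n = 160.

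**Step 2: add clustering at the stated inputs.**
- ICC 0.05: DE = 1 + 7 × 0.05 = 1.35, and 7.75% × √1.35 = 7.75% × 1.16 = 9.0%. Printed: 13%.
- ICC 0.1: DE = 1 + 7 × 0.1 = 1.70, and 7.75% × √1.70 = 7.75% × 1.30 = 10.1%. Printed: 14%.

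**Step 3: what the printed figures would need at n = 160.** DE would have to be (13/7.75)² = 2.82 and (14/7.75)² = 3.27. With m = 8 these correspond to ICCs of (2.82 − 1)/7 = 0.26 and (3.27 − 1)/7 = 0.32, not 0.05 and 0.1.

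**Step 4: other methods at the same target.** None gives 13% and 14% together.

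| Variant (160 randomised) | ICC 0.05 | ICC 0.1 |
|---|---|---|
| t quantile, 19 df | 9.6% | 10.8% |
| Continuity correction | 9.3% | 10.4% |
| DE = 1 + m × ICC | 9.2% | 10.4% |
| DE applied without the square root | 10.5% | 13.2% |
| 99% interval | 11.8% | 13.3% |
| Unequal clusters, CV 1.0 | 10.2% | 12.2% |
| Unequal clusters, CV 1.9 | about 13% | 16.6% |
| 320 eligible, 16 per site | 7.2% | 8.7% |

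The unequal-cluster rows use DE = 1 + [(CV² + 1)m − 1] × ICC. The last row replaces 160 by 160/0.5 = 320 eligible patients.

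**Step 5: which sample size does fit.** With n = 80 and m = 8 (10 sites), the unclustered half-width is 1.96 × √(0.25/80) = 11.0%. Then 11.0% × √1.35 = 12.7% and 11.0% × √1.70 = 14.3%, which round to 13% and 14%. At m = 8, only n = 78 to 82 rounds to both, and 80 is the only total in that range made of whole sites of 8.

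**Step 6: a check that needs no cluster size.** Under a design effect of this form, the squared half-width is linear in the ICC. Extrapolating from 0.1 and 0.05 back to zero gives √(2 × 13² − 14²) = √142 = 11.9%. Allowing for rounding to the nearest percent, the smallest value is √(2 × 12.5² − 14.5²) = √102.25 = 10.1%. If the authors rounded up, it is √(2 × 12² − 14²) = √92 = 9.6%. All exceed the printed 8%, so the three figures cannot describe one sample size. The 11.0% for n = 80 lies inside the nearest-percent range.

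**The case against.** The strongest objection concerns importance. The article disclaims a formal calculation, plans a descriptive analysis without group comparisons, and set no formal progression criteria, so no decision turns on 13% rather than 9%. The error is also conservative: the overall rate would be estimated more precisely than claimed, and the intervals reported at the end will come from the observed data. All of this stands and limits the severity. It does not make the sentence correct.

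A second objection concerns method. The clustered figures cite a source that cannot be consulted here, so the simple design effect is an assumption about how they were obtained. This is fair, but none of the alternatives tried gives the printed pair, and the linearity check does not depend on the cluster size.

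Three stronger readings are tempting and go beyond the article:

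- **That the clustered lines were computed for one formulation.** The fit is close: 80 patients receive each formulation, and sites are allocated 1:1, giving about 10 of the 20. But the article never says so, and the origin remains an inference.
- **That 80 patients in 10 sites is the only match.** This holds at the stated cluster size of 8 and after rounding. Other layouts, such as 72 patients in 12 sites of 6, also round to 13% and 14%, although the article describes none of them.
- **That the right figures are about 7% and 9%, because the denominator should be the eligible patients.** That changes the cluster size from the stated 8 to 16 and is a separate question. It also moves further from the printed values.

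**Conclusion.** The point holds as an arithmetic inconsistency of moderate severity. Under the stated inputs, the half-widths are about 9% and 10% (about 10% and 11% with t on 19 df). The printed values are therefore about 4 percentage points too wide under the normal approximation: 13 − 9.0 = 4.0 and 14 − 10.1 = 3.9. The inflation from clustering at an ICC of 0.05 is √1.35 = 1.16, against the 1.6 or so that a reader would infer from 8% and 13%.

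This rests on the standard design effect with roughly equal clusters of 8, p = 0.5 and a 95% interval. A reader might infer that the target of 160 is inadequate or that the design must change. The article gives no ground for either, because the error understates the overall precision.

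**What to change.** Choose whichever matches the authors' intention:

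1. If overall precision was meant, restate the clustered figures as about 9% (ICC 0.05) and 10% (ICC 0.1) for 160 patients in 20 sites of 8, and keep the unclustered 8%.
2. If per-formulation precision was meant, label 13% and 14% as applying to 80 patients in 10 sites for each formulation, and give the matching unclustered figure of 11%.

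In either case, state the number of patients, the cluster size and the formula behind each figure, and have the authors confirm which calculation was run. The cost is one sentence in the Sample size section. The target, the number of sites and the analysis stay as they are.
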